## Abstract

**Background:**

Hair loss is one of the most common side effects of chemotherapy, and can cause persistent negative emotions, further affecting therapeutic effects and reducing the quality of life. However, there are no clinically safe and effective methods to solve the problem at present. Our previous clinical and animal studies showed that a medicinal and edible decoction, YH0618, could significantly promote hair growth in cancer patients after chemotherapy, without interfering with the anti-tumor effects of chemotherapy. Besides, the theory of Chinese Medicine believes that the “Essence of the kidney is reflected on the hair”. Therefore, this study will further explore the efficacy of YH0618 granule on chemotherapy-induced hair loss in patients with breast cancer by a randomized, double-blind, multi-center clinical trial and elucidate the potential mechanism from the aspect of kidney deficiency or renal dysfunction.

**Methods/design:**

Eligible breast cancer patients who will start chemotherapy will be randomly divided into group A (YH0618 granule) and group B (placebo). The chemotherapeutic agents contain taxanes or/and anthracyclines, and the chemotherapy regimen will be for at least six cycles with a cycle every 3 weeks. Subjects assigned to group A will receive YH0618 granules twice a day (6 g each time), 6 days a week, mixed with 300 ml warm water from the first to the fourth chemotherapy cycle. Subjects in group B will receive the placebo granule in the same manner. The primary outcome is the time point of occurrence of hair loss reaching grade II as assessed by the WHO Toxicity Grading Scale, and objective indices of hair quality and hair-follicle growth recorded by a hair and scalp detector before the fifth chemotherapy cycle. Secondary outcomes include changes of facial color and thumbnail color, grading of thumbnails ridging, assessment of quality life, level of fatigue, routine blood test results, hepatic and renal function, and certain medical indicators which can reflect kidney deficiency in Chinese Medicine.

**Discussion:**

This research is of great significance for the treatment of cancer and improving the quality of life of cancer patients. The study may provide the most direct evidence for meeting clinical needs and lay a solid scientific foundation for later product development.

**Trial registration:**

Chinese Clinical Trial Registry, ID: ChiCTR1800020107. Registered on 14 December 2018.

## Background

Chemotherapy is a major type of cancer treatment using chemical medications to affect cancer cell growth, division and reproduction. Regardless of the route of administration, chemotherapy drugs are introduced into the blood stream, so that chemotherapy can cause various degree of damage to other normal organs and tissues while killing cancer cells, further causing a series of serious adverse effects/toxicity.

Hair loss is an obvious side effect of chemotherapy. The incidence of chemotherapy-induced hair loss is as high as 65% in patients receiving chemotherapy and in some is even up to 80–100% in patients receiving specific agents, such as doxorubicin and docetaxel [1–3]. Although hair loss itself does not cause damage to the body and threaten life, it can induce persistent negative emotions such as anxiety, depression and negative evaluation of self-image, which in turn reduces quality of life [4]. The hair loss caused by chemotherapy is usually reversible; however, in most cases, the color of the new hair is grayish or different from the previous color, and the hair texture also shows some changes, such as being rougher, slower growing and sparser [5, 6]. Besides, contemporary social media and excessive attention to appearance have put more pressure on patients, with 8% of patients saying that they refuse chemotherapy because of fear of alopecia [7]. Even some female patients said that having no hair is more difficult to tolerate than mastectomy [8].

The mechanism of chemotherapy-induced hair loss is still unclear because of the difference between animal models and the actual human body, and the human scalp cannot be extracted for research. The current reported mechanisms of chemotherapy-induced hair loss mainly involve deoxyribonucleic acid (DNA) damage, hair-follicle cell-cycle inhibition, hair-follicle-cell apoptosis, and reactive oxygen species and signal transduction, etc. Accordingly, animal-model studies have found that vasoconstrictors, antioxidants, hair-growth cycle regulators and parathyroid hormone can improve hair loss caused by chemotherapy [9]. In clinical practice, it has been reported that minoxidil, AS101 and vitamin D3 can treat chemotherapy-induced hair loss, but the effect is not significant [10]. Currently, scalp-cooling is the only method approved by the US Food and Drug Administration (FDA) for use for chemotherapy-induced hair loss, and the hypothesis about its mechanism is that the low-temperature-induced rapid contraction of blood vessels can reduce blood flow into hair follicles, and cause a general reduction in cutaneous-cell metabolism, which makes the hair less affected by the chemotherapy [11]. Unfortunately, the success rate of scalp-cooling is also only 50%, and patients with cold allergy, cold agglutination, and cold globulinemia are not suitable for this method [9]. Although some progress has been made in the mechanism, research and management of alopecia, there is no very effective way in solving the hair loss caused by chemotherapy so far. Therefore, it is necessary for clinicians and researchers to pay more attention to chemotherapy-induced alopecia and a series of relevant psychological problems to further elucidate the mechanism of hair loss and develop safe and effective solutions.

YH0618, a medicinal and edible compound prescription, is developed based on the “homology of medicine and food,” theory ancient prescription, and long clinical practice. Our previous animal studies have shown that YH0618 decoction did not interfere with the anti-tumor effects of chemotherapy drugs [12]. Additionally, a randomized clinical trial also showed that YH0618 significantly accelerated hair regrowth and reduced thumbnail pigmentation in cancer patients who have completed chemotherapy (data was not showed, but the protocol was published in [13]). Therefore, this study will further explore the efficacy of YH0618 granule on chemotherapy-induced hair loss in patients with breast cancer by a randomized, double-blind, multi-center clinical trial. YH0618 consists of five medicinal and edible foods (black soybean and liquorice, etc.) which are recommended by clinicians for cancer patients and all components have a history of safe use in other foods. Besides, each of the components possesses a distinct pharmacological profile, including removing free radicals in the body, regulating the immune system, preventing cancer, detoxifying and enhancing the sense of taste [14–16]. Black soybean and liquorice, as the main essential ingredients, have been used for detoxification for millennia in China. Based on the theory of the “Essence of the kidney is reflected on the hair” in traditional Chinese Medicine, the color, texture and growth of hair is believed to be closely related to the kidney. However, there is no in-depth research on the relationship between kidney and hair, and no research is combined with the comprehensive evaluation of renal function from the aspects of both Chinese and western medicine to explore the mechanism of chemotherapy-induced hair loss. The kidney is an important detoxification organ of the human body and helps to filter out toxins in the blood and other waste through urine. Chemotherapy drugs may not cause renal organic lesions, but they “consume” kidney essence and kidney *qi*, which breaks the balance of the body. Therefore, we believe that chemotherapy agents not only directly produce toxic effects on hair-follicle cells, but also deplete *qi*, blood and body fluids, especially kidney essence and kidney *qi*, and breaks the balance of *yin* and *yang* of the human body, which leads to the obstruction of microcirculation and the decline of immune function, further resulting in nutritional disorders of hair follicles and hair loss. Thus, the study will also elucidate the mechanism of YH0618 granule on reducing hair loss from the aspect of kidney deficiency or renal dysfunction. The hypothesis of the study is that YH0618 granules could delay chemotherapy-induced hair loss by improving kidney deficiency and renal dysfunction.

## Methods/design

### Study design

This is a randomized, double-blind, multi-center controlled trial which aims at exploring the efficacy of YH0618 granule on chemotherapy-induced hair loss in patients with breast cancer and elucidating the potential mechanism from the aspect of kidney deficiency or renal dysfunction. To achieve this goal, a total of 214 breast cancer patients who will receive their first chemotherapy will be recruited for the study. The patients will be randomly divided into group A (YH0618 granule) and group B (placebo) using a 1:1 allocation ratio, adhering to the Consolidated Standards of Reporting Trials (CONSORT) Statement [17] and the Standard Protocol Items: Recommendations for Interventional Trials (SPIRIT) Statement [18] (Additional file 1). The primary outcome of this study is the time point of occurrence of hair loss reaching grade II as assessed by the World Health Organization (WHO) Toxicity Grading Scale, and objective indices of hair quality and hair-follicle growth recorded by a hair and scalp conditioner (CBS-603, CBS-Medical Skin Analysis, Taiwan). Secondary outcomes include changes of facial color and thumbnail color, grading of thumbnail ridging, assessment of quality life, fatigue level, routine blood test results, hepatic and renal function, and some medical indicators which can reflect kidney deficiency in Chinese Medicine. The flow chart of the study is shown in Fig. 1 and Table 1. The recruitment, evaluation and data collection will be conducted at Galactophore Department of Guangdong Provincial Hospital of Chinese Medicine, Galactophore Department of The First Affiliated Hospital of Guangzhou University of Chinese Medicine, and Galactophore Department of The Third Hospital of Nanchang.

**Fig. 1 Fig1:**
[figure not shown]
Flow chart of the clinical trial

**Table 1 Tab1:** Trial process chart

	Before baseline screening	Baseline	Visit 1 treatment phase	Visit 2 treatment phase	Visit 3 treatment phase	Visit 4 treatment phase	Visit 5 follow-up phase
		(before chemo)	Before 2nd chemo	Before 3rd chemo	Before 4th chemo	Before 5th chemo	1 month after chemo
Patients							
Inclusion and exclusion criteria	×						
Informed consent		×					
Demographics		×					
Medical characteristics	×	×	×	×	×	×	×
Randomization and allocation concealment		×					
Primary outcomes							
Grading of hair loss		×	×	×	×	×	×
Objective indices (hair quality and hair follicles)		×	×	×	×	×	×
Secondary outcomes							
Facial color and thumbnail color		×	×	×	×	×	×
Grading of thumbnail ridging		×	×	×	×	×	×
Quality of life and fatigue		×	×	×	×	×	×
Routine blood test		×	×	×	×	×	×
Liver function (ALT, AST, total protein, and Alba)		×	×	×	×	×	×
Renal function (Cr, UA and BUN)		×	×	×	×	×	×
Kidney deficiency (IgM, C3、CD4 +, CD8 + Mg^2+^, Cu^2+^, Zn^2+^, Fe^3+^)		×		×		×	
Adverse events			×	×	×	×	×
Patients’ diary records			Every day during the study				

*BUN* blood urea nitrogen, *Cr* creatinine, *ALT* alanine aminotransferase, *AST* aspartate aminotransferase

### Ethics

Ethical approvals have been confirmed from the Institutional Review Board at Guangdong Provincial Hospital of Chinese Medicine (BF2018–100-01), The First Affiliated Hospital of Guangzhou University of Chinese Medicine (ZYYECK【2019】006) and The Third Hospital of Nanchang (2018–011). The trial was registered in the Chinese Clinical Trials Registry with ID: ChiCTR1800020107. Patients will receive a detailed information sheet and complete written consent forms.

The trial is managed by the School of Chinese Medicine, Hong Kong University and data will be supervised by the Data and Safety Monitoring Board (DSMB), which is an independent group of experts that advises funding agency and study investigators. DSMB members include three experts from different fields (western medical sciences, Chinese medicine and statistics). The DSMB is for quality control of this research data and ensures the integrity of the study. The protocol compliance, safety, and on-schedule study progress are also monitored by the DSMB. An auditing trial will be conducted every 3 months and the process will be independent from investigators. Study documents (soft and hard copies) will be retained in a secure location for 5 years after trial completion.

### Subjects

A total of 214 eligible patients will be recruited at different clinical centers. Inclusion criteria include: (1) women with stage-I or -II breast cancer aged between 18 and 75 years; (2) receiving first chemotherapy; (3) planning to receive chemotherapeutic agents containing taxanes or/and anthracyclines; (4) the chemotherapy regimen will last for at least six cycles with every 3 weeks a cycle; (5) adverse events assessed using WHO toxicity classification criteria < grade II; and (6) a life expectancy of at least 6 months. Exclusion criteria are: (1) patients with a medical history of hair transplantation; (2) patients suffering from psoriasis or severe scalp infection; (3) hair loss induced by alopecia areata, alopecia totalis or scalp injury, etc.; (4) pregnancy, lactation or potential pregnancy; (5) allergy to some specific foods, like black soybean; (6) severe cardiac, hepatic, renal, pulmonary and hematic lesions or other diseases which will affect their survival; (7) those who have any severe mental or behavioral disorders who cannot be fully informed; (8) suspected of or with a history of alcohol and/or drug abuse; (9) cannot understand or fill in questionnaires because of cognitive disorders or a low level of literacy; and (10) a variety of factors affecting drug taking and absorption, such as the inability to swallow, chronic diarrhea, intestinal obstruction, etc. Eligible patients will be invited to participate in this study after obtaining their written consent form. All participants will be closely monitored in the study.

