### Estimation of sample size

The primary outcome in this study is the time point of occurrence of chemotherapy-induced hair loss reaching grade II measured by the WHO Toxicity Grading Scale for Determining the Severity of Adverse Events. Our previous results showed that YH0618 could cause the incidence of hair loss grade < II to reach 50% for patients who have completed chemotherapy, and the difference between the incidence of hair loss grade < II in YH0618 group and the control group was 15%. Thus, the difference in proportion between the two groups will be measured by a Z test. To achieve a two-sided, type-I error alpha = 0.05 and power: (1 − beta) = 80%, the minimal number of subject need in each group is 85. We estimated a 20% attrition rate at the end of follow-up; hence, a sample size of at least 107 in each group (214 in total) is planned for this study.

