### Outcome evaluation

#### Primary outcome

The primary outcome is the time point of occurrence of hair loss reaching grade II as assessed by the WHO Toxicity Grading Scale, and objective indices of hair quality and hair-follicle growth recorded by a hair and scalp detector (CBS-603, CBS, Taiwan) before the fifth chemotherapy cycle.

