### Grading of chemotherapy-induced hair loss

The WHO Toxicity Grading Scale is commonly used to monitor and rate the severity of anticancer drug-induced toxicity [19, 20]. The grading criteria for hair loss is shown in Table 2. Alopecia assessments will be conducted by a clinician blinded to treatment assignment, and by the participant.

**Table 2 Tab2:** World Health Organization (WHO) grading criteria for anti-drug induced hair loss

Grade 0	No hair loss
Grade I	Minor hair loss
Grade II	Moderate hair loss/alopecia areata
Grade III	Complete hair loss with regrowth
Grade IV	Non-regrowth hair loss

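### No entry criterion explicitly requires hair loss below WHO grade II at baseline, and the primary test ignores the baseline grade that is collected

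*Protocol article*

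**What the plan says.** The Primary outcome section of the protocol article states: "The primary outcome is the time point of occurrence of hair loss reaching grade II as assessed by the WHO Toxicity Grading Scale". The sample size section ties that instrument to adverse events: "hair loss reaching grade II measured by the WHO Toxicity Grading Scale for Determining the Severity of Adverse Events".

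Three items under Subjects bear on hair at entry:
- Inclusion criterion "2) receiving first chemotherapy".
- Inclusion criterion "5) adverse events assessed using WHO toxicity classification criteria < grade II".
- Exclusion 3, which removes "hair loss induced by alopecia areata, alopecia totalis or scalp injury, etc".

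Table 2 defines grade I as "Minor hair loss" and grade II as moderate loss or alopecia areata.

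In Table 1 the inclusion and exclusion criteria are marked only in the screening column before baseline. Hair-loss grading is first marked at Baseline, in the same column as randomisation. Adverse events are first marked at Visit 1.

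The Statistical analysis section compares hair-loss grading before the fifth cycle by Fisher's exact test. A multivariable logistic model is exploratory. Its covariates are chosen only if they differ between groups at baseline and are significantly related to outcome.

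**The concern.** An endpoint defined as reaching a grade needs every patient to start below that grade. Otherwise some patients have met the event before any chemotherapy or study product, and treatment cannot delay it for them. Here the entry rule that should secure this does not mention hair.

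Patients have not yet had chemotherapy, so chemotherapy-induced loss should be absent at entry. Thinning from other causes can be present in women aged up to 75. A site may or may not call such thinning an adverse event, and may or may not bring it under the open end of exclusion 3. Three centres could answer differently and so enrol different populations.

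Two things are at stake: a small dilution of the arm difference, and a primary comparison that makes no use of a baseline measurement already scheduled.

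**Working it through.** **Step 1: set the provisions side by side.**

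| Provision | What it secures | What it leaves open |
|---|---|---|
| First chemotherapy only | No earlier chemotherapy-induced loss | Loss from any other cause |
| Criterion 5 | WHO grade below II for adverse events | Whether pre-existing thinning counts as one; grade I is allowed either way |
| Exclusion 3 | Three named causes | Other causes, by site judgement; no grade is set |
| Table 1, eligibility row | A check at screening | No hair grade is scheduled by then |
| Table 1, hair-loss row | A grade at Baseline | No stated rule uses it for entry |
| Table 1, adverse-event row | Recording from Visit 1 | Nothing recorded under that name at entry |

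Table 2 also puts alopecia areata at grade II. If criterion 5 were meant as the hair limit, it would already remove such patients, yet exclusion 3 removes them separately. This is suggestive only.

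**Step 2: inputs for the size.** The sample size section gives 50% below grade II on YH0618 and a 15-point difference, so 35% is implied on control. It also gives two-sided alpha 0.05, 80% power, 85 per group, and 107 per group after 20% attrition. It gives no prevalence of baseline hair loss.

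**Step 3: the plan's own figure.** With mean proportion 0.425,

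n = [1.960 × √(2 × 0.425 × 0.575) + 0.842 × √(0.50 × 0.50 + 0.35 × 0.65)]² / 0.15² = 169.3, rounded up to 170 per group.

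The stated 85 is not reproduced. The attrition step is: 85 / 0.8 = 106.25, rounded up to 107. The shortfall is a separate matter. It enters below only because power at 85 per group is already about 51% before any dilution.

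**Step 4: dilution.** Let q be the share in each arm at grade II or worse at entry. Assume that they are counted as not below grade II before cycle 5, and that everyone else follows the planned rates. The rates become 0.50(1 − q) and 0.35(1 − q), and the difference 0.15(1 − q).

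| Assumed q | Difference (points) | Power at 85 per group | n per group for 80% power |
|---|---|---|---|
| 0% | 15.0 | 50.7% | 170 |
| 2% | 14.7 | 49.4% | 176 |
| 5% | 14.25 | 47.3% | 185 |
| 10% | 13.5 | 44.0% | 203 |

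At q = 5% and 10%, the number affected per group is 107 × 0.05 = 5.4 and 107 × 0.10 = 10.7. Grade I patients are below the endpoint and do not enter this calculation.

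**The case against.** The strongest reply is that criterion 5 already does the job. It uses WHO toxicity grading, the term adverse events and the cut-off of the endpoint, and the sample size section describes the endpoint scale in the same terms. In women not yet treated, criterion 5 makes most sense as a limit on baseline condition, hair included. This stands in part: a reader might infer that nothing in the protocol keeps grade II out, and that goes too far. But the reading is not secured while eligibility is checked before any hair grade is scheduled.

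Second, the sample size section calls the event chemotherapy-induced, and Table 2 is headed as grading drug-induced loss. On that view, pre-existing thinning is no event at all. It is true that counting such a patient as a failure is an inference. However, the grades in Table 2 are described by extent and regrowth, with no rule for separating older loss from new loss, and the Fisher test compares the grade as found.

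Third, exclusion 3 is open-ended, and exclusions 1 and 2 also screen for hair and scalp disease. That narrows the gap but leaves its edge to each site.

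Fourth, grade I is below the endpoint, and randomisation spreads these patients over both arms. This stands. A reader might infer that admitting grade I is a fault, or that it dilutes the effect by some known amount. The article supports neither, and no calculation here shows it.

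Finally, a journal article condenses its protocol. But the criteria and the schedule are both printed here, and the point rests on how those two fit together.

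**Conclusion.** The point holds in a limited form. No criterion explicitly requires hair loss below grade II at entry. Criterion 5 can be read to require it, but the schedule in Table 1 and the open cause list in exclusion 3 leave room to randomise a woman who is already at the event. Grade I patients enter on any reading, and the primary Fisher test does not use the baseline grade.

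The size is modest. At an assumed 5% to 10% at grade II, the difference falls by 0.75 to 1.5 points, and power at 85 per group falls by about 3 to 7 points. This assumes that criterion 5 and exclusion 3 stop none of these patients, so it is an upper figure for each assumed prevalence. The true prevalence cannot be taken from the article.

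A reader might also infer that entry must be confined to grade 0. That is a choice of population and is not needed to make the endpoint valid.

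**What to change.** 1. Extend criterion 5 along these lines: *hair loss from any cause must be WHO grade 0 or I, as graded by the blinded clinician at the Baseline visit before randomisation*. The clinician should be named because the article has both a clinician and the participant grade alopecia. With the grade fixed for any cause, the open end of exclusion 3 no longer decides entry at grade II.
2. In Table 1, move the eligibility check to Baseline, or repeat it there after hair grading and before randomisation.
3. Adjust the primary comparison for baseline hair-loss grade (0 or I), fixed in advance rather than selected by observed imbalance. A test stratified by baseline grade, or a logistic model with that grade as a prespecified covariate, would serve. The unadjusted Fisher test can stay as a supporting analysis.
4. Optionally, restrict entry to grade 0 if the sponsor wants a cleaner population.

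The cost is small. The grading is already scheduled, so no measurement is added. Some women would be screened out: at the assumed 5% to 10%, randomising 214 would need 214 / 0.95 = 226 to 214 / 0.90 = 238 Baseline assessments (rounded up), which is 12 to 24 more. The analysis gains one covariate. The entry change cannot help patients already randomised, so it belongs before enrolment.
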